### Summary Study Procedure

Table 3 shows a summary of study procedures, including participant enrollment, interventions, and assessments (Checklist 1).

**Table 3. T3:** Standard Protocol Items: Recommendations for Interventional Trials (SPIRIT) figure of enrollment, interventions, and assessments.

Study procedure	Screening/consent (first visit)	Research episode	28 days’ follow-up electronically
Obtain informed consent where relevant	✓		
Review inclusion/exclusion criteria	✓		
Complete case report form	✓	✓	✓
Collect continuous data from standard care vital sign monitor		✓	
Collect waveform respiratory data		✓	
Review retrospective notes for adverse outcome/available toxicology screen			✓

### Data Collection and Management

CASTOR (The Netherlands) [29] will provide a platform for data collection via an electronic case report form [29]. CASTOR EDC is compliant with 21 CFR Part 11, ICH E6 GCP, GDPR, and HIPAA. It is ISO27001 and ISO9001 certified.

### Safety and Adverse Events

Adverse events and serious adverse events (SAEs) will be managed in line with Good Clinical Practice guidelines. SAEs meeting the above criteria must be reported to the Pharmacovigilance Office immediately (within 24 h) using the SAE form for a non-CTIMP. All SAEs will be reported to the ethics committee within 15 days of the chief investigator or delegate becoming aware of the event.

### Planned Analysis

#### Primary Outcome Measure Analysis

Descriptive statistics will be used to analyze the primary outcome measures and assess the feasibility of studying the use of the PneumoWave device in the three patient groups. The analysis for each primary outcome measure is as shown below.

Length of time the device is in situ on the patient: The time between the documented time the device is placed on the patient and time off the patient will be calculated (seconds). Any time the device was removed will be deducted from the total time. A final analysis of median, mean, and associated IQR and SD will be reported for each group.Number of times the device was removed by the patient or others: This will be reported as median, mean, and associated IQR and SD, respectively, for each group.Ability of the device to collect data while in situ: The amount of data gathered for each episode will be recorded and compared to the length of time the device is in situ on the patient’s body. This will be reported as a proportion. The median, mean, and associated IQR and SD will be reported for each group.

#### Secondary Outcome Measure Analysis

The secondary outcome measures study the data that is captured by the PneumoWave device. In order to analyze this, the device data will be visually reviewed alongside the usual care vital signs and continuous monitoring signs. Respiratory rate calculated from the PneumoWave monitor will be compared to respiratory rate counted by a medical professional from the ETCO_2_ monitor. Accuracy will be analyzed through sensitivity and specificity tests using ETCO_2_ measurements as the gold standard.

Data points in which there has been a change in respiratory pattern, clinical deterioration, clinical intervention, and Glasgow Coma Score will be visually reviewed through time stamp looking at both usual care vital signs and PneumoWave study waveform data. Results will be presented both through written description and visually to highlight waveform changes if applicable.

Analysis of clinician, nurse, and patient opinions on the use of the device will be recorded as median and ranges.

Feasibility was defined as the device remaining attached to the chest with two or fewer removals during the monitoring period and achieving data capture for more than 75% of the total wear time.

The statistical analysis will be performed using MiniTab.

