### Objectives

The primary objective of this study was to assess the feasibility of collecting respiratory waveform data using the PneumoWave device in ED patients from groups 1‐3 (see Study Population).

Secondary objectives of the study were as follows: (1) Collate respiratory data from the PneumoWave device and compare to ETCO_2_ in patients from all 3 groups. Respiratory data will observe normal respiratory effort, reduced respiratory effort due to sedating drugs or anesthetic agents, and response to treatments and interventions required in patients with reduced respiratory effort. (2) Collate waveform and motion artifact data from the PneumoWave device in patients from all 3 groups to observe the relationship with the individual’s conscious level. (3) Assess the usability of PneumoWave in the opinion of the clinician, nurse, and patient. (4) Understand the feasibility of gathering respiratory data from a wearable respiratory monitoring device in the ED.

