### Outcome Measures

The primary outcome measures will measure the length of time the device is in situ on the patient, the number of times the device is removed by the patient or others, and the ability of the device to collect data while in situ. The secondary outcome measures will observe waveform data from the PneumoWave device and compare those with normal care vital signs and continuous monitoring vital signs extracted from patient monitors. PneumoWave respiratory wave patterns and motion artifact will be compared to clinical events, including normal respiratory patterns, clinical deterioration, and interventions in ED or in anesthetic room in theater, and Glasgow Coma Score.

Stakeholders will be interviewed regarding the usability of the device. These stakeholders are the clinician and nurse caring for the participating patient in question, and the patient themselves, if able to.

Outcome measures and their associated data sources and data capture are shown in Table 2.

**Table 2. T2:** Outcome measures and associated data source and data to be collected.

Outcome measure	Data source	Data to be collected
Primary outcome measures		
Length of time the device is in situ on patient	CASTOR EDC [29]	The total time device present on chest as documented by researcher (seconds)
The number of times the device is removed by the patient or others	CASTOR EDC	Absolute number of times the device was removed
The ability of the device to collect data while in situ	PneumoWave sensor	Total amount data recorded (seconds) as the proportion of time the device was on chest (seconds)
Secondary outcome measures		
PneumoWave device waveform data comparison to clinical events	PneumoWave device and CASTOR EDC	Visual representation of PneumoWave data and comparison to the following: ETCO_2_^a^ waveforms Documented respiratory rate Interventions GCS^b^
Usability of device	CASTOR EDC	Data from results of interview reported in Likert scale from 1 to 5.

a ETCO_2_: end-tidal carbon dioxide.

b GCS: Glasgow Coma Score.

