## Discussion

### Expected Principal Findings

The anticipated main finding of this feasibility study is that the PneumoWave wearable respiratory monitoring device will successfully gather respiratory waveform data and will be well tolerated by patients at risk of drug-related respiratory depression. Specifically, it is expected that the device will provide high-quality respiratory waveform data comparable to the gold standard of ETCO_2_ monitoring within the relative safety of the hospital environment [27]. These findings would support the feasibility of using wearable respiratory monitoring to enhance clinical surveillance in populations at risk of respiratory compromise.

The study will allow understanding of the ability of the device to measure respiratory rate and detect changes to a patient’s condition accurately. Apnea can be difficult to study, and in hospitals, it is often brief, as intervention is swift while in the care of medical professionals due to substantial risk of harm if left untreated. Therefore, insight into the feasibility of studying this will be invaluable.

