### Strengths and Limitations

A key strength of this feasibility study is its pragmatic design, enabling evaluation of the PneumoWave device in the ED or anesthetic room, where risk to the patient can be minimized. However, several limitations should be acknowledged. Recruitment challenges are anticipated due to legal restrictions under Scottish Adults with Incapacity laws, which preclude consent via a professional legal representative; this constraint may particularly impact enrollment in the acute toxicology cohort (Group 1). This study has, however, been designed to improve patient outcomes who are at risk of drug-induced respiratory depression and inform future development of clinical support and prediction capability. The study will not be powered to assess diagnostic accuracy or clinical outcomes, and conclusions will therefore be limited to feasibility, tolerability, and data acquisition parameters.

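### Sensor and capnography respiratory rates are both numeric, yet the only accuracy statistic named is sensitivity and specificity, with no yes/no event defined

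*Protocol article*

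**What the plan says.** Under Objectives, the first secondary objective is: "Collate respiratory data from the PneumoWave device and compare to ETCO_2_ in patients from all 3 groups". Table 2, under Outcome Measures, describes the matching data as "Visual representation of PneumoWave data and comparison to the following", followed by ETCO2 waveforms, documented respiratory rate, interventions and Glasgow Coma Score. It gives no rate cut-off, apnea duration or agreement statistic.

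The Secondary Outcome Measure Analysis section has two consecutive sentences on rate. The first: "Respiratory rate calculated from the PneumoWave monitor will be compared to respiratory rate counted by a medical professional from the ETCO_2_ monitor". The second: "Accuracy will be analyzed through sensitivity and specificity tests", with ETCO2 taken as the reference standard. The other waveform comparisons there are visual and descriptive.

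Two Discussion passages bear on how the result will be read. Expected Principal Findings says: "The study will allow understanding of the ability of the device to measure respiratory rate and detect changes", and the sentence goes on to say that this is to be done accurately. Strengths and Limitations says: "The study will not be powered to assess diagnostic accuracy or clinical outcomes, and conclusions will therefore be limited to feasibility, tolerability", with data acquisition parameters added to that list.

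**The concern.** Sensitivity and specificity apply when device and reference each return a yes or a no. Here each returns a rate per minute. The analysis cannot be computed until someone chooses an event, and the article names none. The device does not supply one either: Wearable Technology describes the data-collection product as delivering unprocessed accelerometer data, with the event-detecting algorithms still in development.

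Choosing a cut-off would make the measures computable but would not make them measures of agreement. With a cut at 10 breaths/min, a sensor rate of 22 against a true rate of 16 counts as fully concordant, because both are not low. At stake is the secondary objective of comparing the sensor with ETCO2. The study could end without stating by how many breaths per minute the sensor is off, or in which direction. Amendment NSA01 added a retrospective clinician count to make the reference rate more accurate, and dichotomizing it gives up much of that gain.

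Timing adds to this. Recruitment is complete and the Results section says analysis is in progress. The same data also feed the predictive algorithms. An event chosen after seeing both data sources would tend to flatter the device.

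**Working it through.** The article gives no figure for this analysis (no precision target, cut-off or margin), so there is nothing to reproduce. The steps below test whether the named measures can carry the comparison. All simulation inputs are assumptions.

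**Step 1. Is a binary target defined?** Objectives, Table 2, Source Data Collection and the secondary analysis section give no rate threshold, apnea length or reading window. The 10-second apnea in the Introduction describes another study's device. Result: no target is defined.

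**Step 2. Can two sensors with different agreement share the same sensitivity and specificity?**
- Assumed reference rate: normal, mean 14, SD 4, truncated at 0; 400,000 draws.
- Sensor A: reference plus error with mean 0 and SD 1.5.
- Sensor B: as A, but reading 8/min too high whenever the reference is 16 or more.
- Sensitivity = share of reference-low readings that the sensor also calls low. Specificity = share of reference-not-low readings that the sensor calls not low. Limits of agreement = mean difference ± 1.96 × SD of the differences.

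| | Cut 8 (sens/spec) | Cut 10 | Cut 12 | Bias | 95% limits |
|---|---|---|---|---|---|
| A | 0.80/0.97 | 0.82/0.95 | 0.85/0.92 | 0.0 | -2.9 to +2.9 |
| B | 0.80/0.97 | 0.82/0.95 | 0.85/0.92 | +2.5 | -5.4 to +10.3 |

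B's error lies well above every cut-off, so classification never sees it.

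**Step 3. Does the undefined cut-off matter?** Take a sensor with constant bias +2 and error SD 1.5. Sensitivity is 0.43, 0.48 and 0.54 at cuts of 8, 10 and 12, with specificity 0.99 or higher throughout. Bias is +2.0 with limits -0.9 to +4.9 whatever the cut. The accuracy figure thus depends on a choice that the article does not make.

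**Step 4. What does the planned pair reveal about a constant over-reading?** Assume reference mean 16, SD 4, cut below 10 (about 7% of readings low) and error SD between 1 and 2. At +3/min, specificity is at least 99.7% and sensitivity roughly 21% to 29%. At +6/min, specificity is 100% and sensitivity about 3% to 5%. The pair does signal failure here, through sensitivity. It still does not say whether the sensor is off by 3 or by 6.

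**Step 5. Would repeated readings matter?** Source Data Collection describes continuous data, up to 1 hour in group 1, so several readings per patient are likely. Their number is not given. Design effect = 1 + (m - 1) × ICC, where m is readings per patient. Patients not withdrawn: 25 + 38 + 12 = 75. The 95% half-width at a proportion of 0.90 is 1.96 × √(0.09 × design effect / (75 × m)); ignoring clustering sets the design effect to 1.
- m = 5, ICC 0.1: design effect 1 + 4 × 0.1 = 1.4; half-width 0.030 ignoring clustering, 0.036 allowing for it.
- m = 60, ICC 0.5: design effect 1 + 59 × 0.5 = 30.5; half-width 0.009 against 0.048.

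This matters only if readings are pooled and an interval is reported. The article states neither.

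**The case against.** The strongest reply is that the two analysis sentences need not be one method. The first says only that the rates will be compared, and an agreement summary could sit behind it in the full protocol or SAP. The second may aim at event detection: a secondary end point refers to the device's sensitivity and specificity, the ALERT product is meant to detect concerning breathing, and group 3 was added because apnea is likely at induction. This partly stands. Sensitivity and specificity are legitimate for a named apnea or low-rate event. But the article ties them directly to the rate comparison, calls the result accuracy, and names neither an event nor any other statistic.

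A reader might infer three stronger points that the document does not support:
- **That the plan ignores repeated readings.** It is silent on unit of analysis, pooling and intervals, details commonly left to the full protocol or SAP. Clustering is a reason to choose the right form of the remedy and is not itself an error in the text.
- **That a badly biased sensor would look excellent.** For constant over-reading this holds only if sensitivity is left out. Step 4 shows the planned pair exposing it.
- **That the Discussion flatly contradicts itself.** Estimating accuracy descriptively without power is not contradictory. Expecting accurate rate measurement while limiting conclusions to feasibility, tolerability and data acquisition is a tension that an edit can settle.

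**Conclusion.** The concern holds in limited form. For two numeric rates, the only named accuracy statistic is one that needs a binary event, and none is defined. As written the analysis cannot be computed, and no choice of cut-off would let it show the size or direction of the rate error. The plan therefore does not establish how well the sensor rate matches capnography.

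The textual finding rests on no assumption. Its numerical size does: the identical sensitivity and specificity with limits of -2.9 to +2.9 against -5.4 to +10.3 breaths/min come from assumed rate distributions and errors, with sensor B built to make the point. They show what can happen, not what this device does. The clustering figures are likewise hypothetical.

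The point should be fixed but is not critical. It concerns a secondary analysis that the article says is not powered, and the primary measures and the feasibility rule (removals and data capture) do not depend on it.

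**What to change.** 1. In the Secondary Outcome Measure Analysis section, make agreement the method for the rate comparison: mean bias and 95% limits of agreement (Bland-Altman) for time-matched sensor and ETCO2-counted rates, by group. Use the repeated-measures version with patient as a random effect, and state the reading window and unit of analysis.
2. Keep sensitivity and specificity only as exploratory results for a named low-rate or apnea event, defined before the device and ETCO2 data are compared. If that comparison has already begun, say so and label the definition post hoc. Allow for patient-level clustering in any interval reported.
3. In Expected Principal Findings, label the expectation about accurate measurement of respiratory rate as exploratory, so that it agrees with Strengths and Limitations.

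The cost is analysis-plan wording and a few hours of programming on data already collected. The downside is that the limits may be wider and less favourable to the device than a sensitivity and specificity pair suggests.

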### Study Hypothesis

The PneumoWave device will be well tolerated by patients and will successfully capture respiratory effort and patient movement accelerometer data.

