### Sample Size and Rationale

This is a feasibility study to generate data for future prospective interventional studies; therefore, no formal sample size will be generated. The research group planned a target of 50 patients recruited to both groups 1 and 2 as the number of minutes of data capture would successfully answer the primary outcome question of feasibility. Group 3 was included following trial commencement. Following evidence of the volume and type of data being produced from groups 1 and 2, a target of 12 was used based on the understanding of the number of minutes of data gathered. We aim to recruit a total of 112 patients to the study, which will provide adequate data to establish feasibility of use for larger studies. The sample size breakdown is as follows: group 1: 50 patients; group 2: 50 patients; and group 3: 12 patients.

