### Source Data Collection and Patient Observation

Source data will be collated from multiple sources, including study participant interviews; usual care electronic health records; anesthetic charts; medical, ambulance, and nursing notes; drug charts; and observation charts. Continuous vital sign data will be downloaded from the standard ED or anesthetic monitors or study monitors, PneumoWave sensor data, and manual respiratory rate for study periods using ETCO_2_ monitor.

During the study episode, data will be collected from the above sources for a period of time specific to each group. Data are all gathered by the researcher. Group 1 patients will be observed by the research team member for 1 hour or from commencement of data collection until they are discharged or moved from the ED, whichever is shorter. Group 2 participants will be observed for the duration of their procedural sedation, length of which may vary, and recovery period for up to 15 minutes. Data are gathered from group 3 participants prior to their GA while in the theater’s anesthetic room, during induction of anesthesia and until the patient is moved to the theater.

Usability is investigated by interviewing stakeholders (patient, nurse, and clinician) following each respective research study episode. It is expected that due to the nature of the study, it may not be possible to gather these data for all patients recruited due to reduced conscious level. Responses to domains were on a scale of 1 (least positive) to 5 (most positive). The domains that were investigated were perceptions on device comfort, device intrusiveness, device safety, delay to treatment, acceptability of device in normal practice.

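### Median and range alone can hide a large share of poor usability ratings on the 1-5 scale once a single respondent scores 1

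*Protocol article*

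**What the plan says.** Usability is the third secondary objective in the protocol article: "Assess the usability of PneumoWave in the opinion of the clinician, nurse, and patient". Under Source Data Collection and Patient Observation, the patient, nurse and clinician are interviewed after each study episode on five domains: "perceptions on device comfort, device intrusiveness, device safety, delay to treatment, acceptability of device in normal practice". Each is scored from 1, the least favourable answer, to 5, the most favourable. Table 2 under Outcome Measures describes the same item: "Data from results of interview reported in Likert scale from 1 to 5".

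The Secondary Outcome Measure Analysis section gives the whole stated analysis of these ratings: "Analysis of clinician, nurse, and patient opinions on the use of the device will be recorded as median and ranges". It mentions no frequency table, interquartile range or share of low scores.

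The Study Hypothesis, on which the ratings bear, opens with "The PneumoWave device will be well tolerated by patients". The article also warns that, for the usability interviews, "it may not be possible to gather these data for all patients recruited due to reduced conscious level".

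**The concern.** On a five-point scale the minimum and maximum are set by the two most extreme raters. The median shows only where the middle rater sits. Neither says how many respondents were dissatisfied. One score of 1 and one of 5 stretch the range over the whole scale, and from then on it carries no further information. The median can stay at 4 or 5 until half of the ratings are poor.

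At stake is how well the study can answer its third secondary objective and support the tolerability part of its hypothesis. A reader given a median of 4 and a range of 1-5 cannot tell whether one person or nearly half of the respondents found the device uncomfortable, intrusive or unacceptable. The article fixes this summary itself, so the point is not about detail left to a fuller document.

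**Working it through.** **Inputs from the article.** The scale is 1-5, with 5 most favourable. Planned sizes (Sample Size and Rationale) are "group 1: 50 patients; group 2: 50 patients; and group 3: 12 patients", and 50 + 50 + 12 = 112, which reproduces the stated total. Enrolment after withdrawals (Results) is 25 in group 1, 39 - 1 = 38 in group 2 and 14 - 2 = 12 in group 3. The article gives no power, threshold or margin for usability, so there is no planned usability figure to reproduce.

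**Step 1: two sets of 25 ratings with the same planned summary.** The median of 25 is the 13th ordered value.

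| | Set A | Set B |
|---|---|---|
| Ratings | nine 1s, three 2s, eight 4s, five 5s | one 1, one 3, thirteen 4s, ten 5s |
| 13th ordered value (median) | 4 | 4 |
| Range | 1-5 | 1-5 |
| Scores of 1 or 2 | 12/25 = 48% | 1/25 = 4% |
| IQR (7th to 19th value) | 1-4 | 4-5 |

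The planned report is the same for both sets. The IQR or the counts separate them.

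**Step 2: how far this goes at each size.** The largest number of low scores that leaves the median at 4 or 5 is floor((n - 1)/2). The smallest number that gives a minimum of 1 is one.

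| n | Smallest low share with minimum 1 | Largest low share with median 4 or 5 |
|---|---|---|
| 12 | 1/12 = 8% | 5/12 = 42% |
| 25 | 1/25 = 4% | 12/25 = 48% |
| 38 | 1/38 = 3% | 18/38 = 47% |
| 50 | 1/50 = 2% | 24/50 = 48% |

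A median of 4 with a range of 1-5 is compatible with both ends of each row and with every count between them.

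**Step 3: how likely the condition is.** The ambiguity needs at least one score of 1 for the well-rated device. If a proportion p of raters score 1, independently, the chance is 1 - (1 - p)^n. The article gives no p, so a range is assumed.

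| n | p = 2% | p = 5% | p = 10% |
|---|---|---|---|
| 12 | 22% | 46% | 72% |
| 25 | 40% | 72% | 93% |
| 38 | 54% | 86% | 98% |

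For example, 1 - 0.98^25 = 0.397. These sizes are upper limits on patient respondents, because the article expects some patients to be unable to answer. Fewer respondents lower each figure.

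**Step 4: the opposite case.** If nobody scores low and the range is 4-5, median and range do show that the device was well rated.

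**The case against.** Median and range is a conventional summary for ordinal data, and this is a descriptive secondary outcome in a feasibility study without a formal sample size. No decision depends on the usability median: the stated feasibility definition uses only removals and data capture. Set A is also close to the worst case by construction. All of this stands, and it limits the weight of the point.

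Several stronger readings are tempting, but the documents do not support them:

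- *Median and range can never tell a good device from a poor one.* They can when nobody scores 1. With an assumed 2% scoring 1, no such score is the likelier outcome at 12 raters (78%) and at 25 (60%).
- *Usability is singled out for a weaker summary than everything else.* The IQR and SD in the Primary Outcome Measure Analysis section apply to the three primary outcomes. The other secondary outcomes are handled by visual review, written description, or sensitivity and specificity.
- *The tolerability hypothesis rests on these ratings alone.* Time in situ and number of removals are primary outcomes that also bear on tolerance.
- *The groups will be compared on ranges that depend on group size.* The article plans no such comparison of usability.
- *Missing patient ratings are an undisclosed bias.* The article says they are expected, and it also collects nurse and clinician ratings. Splitting those ratings by whether the patient could respond would be optional detail.

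One might also read ranges as interquartile ranges, which would remove most of the problem. The article does not say so, and it writes IQR in the preceding section where it means that.

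**Conclusion.** The point holds as a minor-to-moderate weakness. Once one respondent scores 1, the stated summary can be the same for a device with about 3-8% poor ratings and one with about 42-48%, at the enrolled group sizes of 38, 25 and 12. Across assumed rates of 2-10% for a score of 1, that condition arises with probability of about 22-72%, 40-93% and 54-98% at 12, 25 and 38 raters.

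This rests on reading ranges as minimum to maximum, on the assumed rates, on independent raters, and on group sizes that are upper limits for patients. It does not show that the ratings will be misleading, or that the tolerability conclusion lacks other support. It shows that the chosen summary discards information already collected that would answer the usability objective better.

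**What to change.** In the Secondary Outcome Measure Analysis section, replace the median-and-range summary with the count and percent at each score from 1 to 5, plus median and IQR. Report these by domain, group and respondent type, with the number responding in each cell.

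No new data are needed, because the individual scores are already collected, and the article reports that analysis is still in progress. The cost is one changed sentence and a longer table.
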